**FIGURE 3 F3:**
[figure not shown]
ATOP recruitment overview-Takiwasi (as of Dec. 17, 2020).

A related challenge that is important to account for in the study design and analysis is the level of treatment exposure for those formally accepted into the study cohort after the initial ayahuasca experience. We approach the measurement of treatment exposure in two ways. First, with respect to treatment completion the study cohort is divided into three sub-groups: 1) completed treatment; 2) left the program prematurely but voluntarily; and 3) suspended from the program. For the current 12-months sample of 48 clients, the number in each group is 30 (60%); 14 (29%); and 4 (8%), respectively. While all three sub-groups are included in the discharge and follow-up samples, the number of weeks of treatment participation is calculated for each patient. The second approach to measuring treatment exposure is based on an extract of information from the patient files concerning the nature and extent of participation in program activities, for example, the number of ayahuasca sessions, days of dieta, integration sessions with staff. A program participation index will be calculated from these extracted data, also for inclusion in the analysis.

To investigate the potential for response bias in our study sample due to early or subsequent treatment drop-out, a process has been undertaken to locate clients who left prematurely in order to explore reasons for leaving the program. At the time of this writing, the questionnaire has been drafted (see Supplementary Material) and the survey is being mounted for on-line completion. Once finalized, those recruited for the study who have left prematurely will be contacted using the last available email address and a request made for completion of the questionnaire. Also, characteristics of program completers and non-completers will be compared (e.g., age, country of origin; results of the intake psychiatric interview and/or other baseline data).

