#### Analysis Plan

While the details of the analysis plan differ significantly for the qualitative and quantitative components of the mixed methods, they share several common elements: 1) guided by specific pre-determined research questions in support of the broader project goals identified above; 2) undertaken by two analytic teams working independently and according to their area of expertize (i.e., qualitative or quantitative) but meeting bi-weekly as a unified project team to discuss progress, and develop a consensus on critical questions and issues brought to the meeting from each team.

With respect to the research questions guiding the analysis, these questions were developed by the overall team to create an overarching analytic framework, with the quantitative and qualitative analyses contributing differentially to each question. For example, with respect to Takiwasi patients, both quantitative and qualitative analyses were aimed at the following questions:• What is the individual’s previous experience with substance use treatment and what learnings and challenges are being brought into this new experience at Takiwasi? Is previous treatment experience associated with treatment outcomes?• What is the individual’s situation at treatment entry with respect to physical and mental health challenges and overall life satisfaction? Are baseline physical and mental health challenges associated with treatment outcomes?• What meanings are attached to the overall Takiwasi treatment experience as well as key elements (e.g., treatment milieu, specific medicines, dieta, purging, icaros, therapeutic integration) and how have these meanings evolved during the course of the program? What ratings attached to the significance of these experiences are most closely associated with treatment outcome?

The key questions specific to the quantitative analysis are:• What are the outcomes achieved at 12 months post-discharge (e.g., self-reported reduction in substance use and overall addiction severity; improvements in symptoms of anxiety and depression; change in overall quality of life)?• What factors are independently associated with these 12-months post-discharge outcomes (e.g., treatment motivation; baseline addiction severity or mental health status; discharge status on improvements in mood and anxiety or spirituality).

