Post-discharge outcomes relative to baseline will be analyzed with a generalized linear mixed effects model. Random intercepts (and random slopes where necessary) will be included to account for correlation between observations within study participants. The regression models will also include (potentially time-varying) baseline and within-treatment covariates (e.g., treatment motivation, baseline addiction severity, and number of hours engaged in non-ayahuasca treatment activities such as psychotherapy, group integration, ergotherapy). Statistical inference will proceed in a manner consistent with the DAGs constructed before any models are fit. The relevant parameter and variance estimates associated with all models that are fit will be reported.

*Qualitative analytics—Patients* The qualitative team is composed of four researchers, two of which are native Spanish-speakers, and the other two speak Spanish at an expert level. Qualitative analysis will employ a grounded theory approach (Miles and Huberman, 1994; Strauss and Corbin, 1994), in which the team creates codebooks based on themes that emerge from the interview data with inpatients. Grounded theory approaches work best with relatively open-ended questions and narratives which allow for deep analysis and emergence of key themes, which ultimately become integral to building a case-specific theory about outcomes related to set and setting at Takiwasi. In line with this approach, the original guiding research questions may be modified in an iterative process according to significant themes that emerge in the data.

The team selected a cloud-based qualitative data analysis program (www.dedoose.com) through which they can remotely cross-code data and conduct collaborative analyses. Analysis will focus on several themes guided by the specific research questions, including recovery capital, expectations and perceptions of treatment, spirituality, religiosity, and social influences, among others.

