### Limitations and Conclusion

It is important to highlight some of the limitations of the study protocol in achieving its ambitious goals. Despite the many strengths of studying ayahuasca-assisted treatment in a naturalistic setting, there are some uncontrolled factors that hinder our ability to suggest precise conclusions about efficacy. For example, the precise composition of the ayahuasca tea and the dosage of consumption (ml/kg) are not available. Similarly, we could not measure the phenomenological strength of the psychedelic experience (e.g., Barrett et al., 2015). Further, the basic study design precludes strong statements of causality, although it’s important to note considerable expert opinion in the field of psychedelic science about the limitations of clinical trials in studying these complex interventions that are so heavily dependent on treatment context. And while our protocol may identify particular aspects of treatment context that could potentially be manipulated in an experimental design, we remain very cognizant of the perspective of healers experienced with this traditional medicine that the healing potential is in the “gestalt” of the practice and the participant’s experience (Berlowitz et al., 2018).

Lastly, we note the high rate of program not-completion, a factor common to TC’s and clearly a concern with respect to Takiwasi Center specifically and a source of potential bias. To mitigate this concern to the extent possible, a sub-project has been initiated to follow-up with all Takiwasi study patients who have left the program prematurely to explore reasons for leaving the program. The study protocol also includes a variable that measures length of program participation and which will be used a potential moderating variable in the multivariate analysis. Aside from controlling for potential bias, we also view this as an important aspect of the study itself given positive outcomes that have been obtained with a single dose of ayahuasca (Osório et al., 2015; Sanches et al., 2016; Palhano-Fontes et al., 2018), and potential implications for Takiwasi and other ayahuasca-assisted treatment modalities.

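### Baseline predictors risk being adjusted for in-treatment and discharge variables on their own path to the 12-month outcome, and length of stay cannot control drop-out bias

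*Protocol article*

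**What the plan says.** All references are to the protocol article.

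- **Model.** Under Analysis Plan, "Post-discharge outcomes relative to baseline will be analyzed with a generalized linear mixed effects model". The covariates are described thus: "The regression models will also include (potentially time-varying) baseline and within-treatment covariates". The examples given are treatment motivation, baseline addiction severity and "number of hours engaged in non-ayahuasca treatment activities such as psychotherapy, group integration, ergotherapy".
- **Question.** The same section asks: "What factors are independently associated with these 12-months post-discharge outcomes". Its list of examples puts motivation and baseline severity or mental health next to "discharge status on improvements in mood and anxiety or spirituality".
- **Model building.** DAGs are drawn before fitting, and inference is to be consistent with them. The roles named in the DAGs are predictor, moderator and outcome. Regressions start from DAGs of three to five variables and are enlarged according to variance explained, with regard to power.
- **Exposure.** Under Study Recruitment and Measuring Treatment Exposure, "the number of weeks of treatment participation is calculated for each patient", and "A program participation index will be calculated from these extracted data, also for inclusion in the analysis".
- **Drop-out.** Limitations and Conclusion raises non-completion as a source of bias. In response it offers a survey of premature leavers and a length-of-participation variable that "will be used a potential moderating variable in the multivariate analysis". The next sentence treats controlling bias as one purpose of that variable.

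**The concern.** Hours of therapy, weeks in residence and improvement by discharge all arise after baseline. A more motivated or less severely affected patient may stay longer, take part more and be better at discharge, and each of these may carry through to 12 months. The article itself cites a review in which treatment completion was the strongest predictor of later abstinence (section on long-term residential programs).

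If such a variable sits in the model with motivation or severity, the baseline coefficient no longer measures the whole association with outcome. It measures only what remains once the route through participation is held fixed. If something unmeasured affects both staying and outcome, conditioning on staying also adds collider bias.

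The Abstract sets out to learn why, how and for whom the programme works. For whom needs the total association, and the plan never says whether a coefficient is meant as total or direct. A baseline characteristic could be reported as unimportant because its effect was adjusted away. Length of stay could look therapeutic because patients who are doing well stay.

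**Working it through.** The document gives no sample size, power or effect size for these models, so there is no design figure to reproduce. The check has three parts.

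**1. Who a length-of-stay term can reach** (counts from Study Recruitment and Measuring Treatment Exposure)

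- Completed intake: 128. Left before any ayahuasca: 42, and 42/128 = 32.8%, as printed. Cohort: 128 − 42 = 86.
- Due for one-year follow-up: 60. Completed both interviews: 48, and 48/60 = 80%, as printed. Without complete 12-month data: 60 − 48 = 12.
- Within the 48: 30 completers, 14 voluntary leavers and 4 suspended, so 14 + 4 = 18 did not complete.

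Length of stay varies across those 48 and can describe how outcome differs with it. A covariate in the outcome model does not supply outcomes for the 42 outside the cohort or for the 12 not fully observed.

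**2. Effect of adjusting for a variable on the path** (all path values assumed)

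Let X be a baseline predictor, M a post-baseline variable and Y the 12-month outcome, with paths a (X to M), b (M to Y) and c (X to Y directly). In a linear model the total coefficient of X is c + ab, and the coefficient adjusted for M is c. The share lost is ab/(c + ab).

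| a | b | c | Total | Adjusted | Lost |
|---|---|---|---|---|---|
| 0.2 | 0.3 | 0.2 | 0.26 | 0.20 | 23% |
| 0.3 | 0.3 | 0.2 | 0.29 | 0.20 | 31% |
| 0.3 | 0.5 | 0.2 | 0.35 | 0.20 | 43% |
| 0.5 | 0.5 | 0.2 | 0.45 | 0.20 | 56% |
| 0.4 | 0.4 | 0.1 | 0.26 | 0.10 | 62% |

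Now add an unmeasured cause of both M and Y, with path u = 0.4 to each and X and M at unit variance. The adjusted coefficient becomes c − au²/(1 − a²).

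- a = 0.3: 0.2 − 0.048/0.91 = 0.147, against a total of 0.29 (b = 0.3) or 0.35 (b = 0.5).
- a = 0.5, b = 0.5: 0.2 − 0.08/0.75 = 0.093, against 0.45.
- a = 0.3, b = 0 (M has no effect on Y): the total is 0.20 and the adjusted value is still 0.147.

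Simulation with 2,000,000 observations returned the same values.

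**3. Whether the model-building rule would keep a mediator**

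In the same simulation (c = 0.2, a = 0.3, u = 0.4, residual SD of Y 0.7), adding M raised R² from 0.09 to 0.32 when b = 0.3, and from 0.11 to 0.46 when b = 0.5. At n = 48, over 20,000 runs, M met p < 0.05 in 95% and 99.9% of runs respectively. Under these assumptions, a rule based on variance explained nearly always admits the mediator.

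**The case against.** The strongest reply is the DAG commitment. DAGs exist to separate mediators and colliders from confounders, and the plan ties inference to DAGs drawn before any fitting. The example DAG is in a supplement that is not shown. A reader might infer that the baseline coefficients will certainly be over-adjusted; the text does not establish that. Nor does it put discharge status in every model. Discharge status appears as an example within a research question, and length of stay is only a potential moderator. This part of the reply stands, and it reduces the point to a risk.

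It does not remove the risk. The roles named for the DAGs leave out mediators, and enlarging a model by variance explained is a different principle from choosing an adjustment set from a DAG.

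Second, a coefficient adjusted for a mediator is wrong only if read as a total effect. The question asks about independent association, and the article disclaims strong causal statements. That also stands, but the plan does not say which reading applies.

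Third, on drop-out, premature leavers are kept in the follow-up samples, and a leaver survey and a completer comparison are planned. These help to describe the bias. They do not make length of stay a correction for it.

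A reader might also infer that the participation index merely restates weeks in residence. One simulation, assuming 70–100% attendance on the stated schedule, gave a correlation of 0.98 and a variance inflation factor of about 28. With attendance varying by person the figures were 0.93 and about 8, and at 40–100% attendance 0.78 and about 2.6. The index formula is not given, and nothing says that the index and weeks enter one model. These are illustrations only, and the index is a secondary matter.

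**Conclusion.** The point holds as a risk that the current wording leaves open. The plan mixes baseline and in-treatment covariates in the same models, offers discharge status as one more independent factor, names no mediators and enlarges models by variance explained. Baseline coefficients from such models would mislead if read as total associations. The 23% to 62% range rests wholly on assumed paths in a linear model, with no unmeasured common cause in the table. With one, the loss can be larger: 0.45 falls to 0.09 in the most extreme case tried. The document supplies none of these path values, so no single figure should be quoted as the expected bias.

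The statement on length of stay is firmer, because it does not depend on any path value. Whatever DAG is drawn, a covariate measured after entry cannot correct for the 42 who never joined the cohort or the 12 without complete 12-month data.

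**What to change.** 1. Estimate each baseline predictor in models that contain baseline covariates only, and label the coefficient a total association.
2. Fit separate models for in-treatment and discharge factors, adjusted for baseline motivation, severity and mental health and, where the DAG requires it, for the other treatment components.
3. Name the mediators in the DAGs and take covariates from the resulting adjustment sets, in place of the variance-explained rule.
4. Delete the claim that length of stay controls drop-out bias. Report it as an association open to reverse causation.

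Expressing participation as a rate per week, with weeks kept separately, is optional. It separates intensity from duration but sets aside cumulative exposure.

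The cost is a few more models on data already collected, some rewording, and fewer factors shown side by side in one table.

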## Discussion

Considerable research has pointed to the therapeutic value of ayahuasca and ayahuasca-assisted treatment for substance use disorders (Thomas et al., 2013; Bouso and Riba, 2014; Nunes et al., 2016; Argento et al., 2019) as well as other mental health challenges, in particular depression and anxiety (Osório et al., 2015; Tupper et al., 2015; Palhano-Fontes et al., 2018; Muttoni et al., 2019), many of which co-occur with problematic substance use (Chan et al., 2008). This interest in ayahuasca coincides with a resurgence in interest and research in psychedelic medicine, including chemically similar pharmacological compounds such as LSD and pharma-grade psilocybin (Muttoni et al., 2019; Brierley and Davidson, 2012). Research on ayahuasca also represents a growing interest in traditional medicine in general, which includes, but is by no means limited to, other entheogens such as peyote, ibogaine, and psilocybin mushrooms. Indeed, ayahuasca is poized to be situated on the bridge between ancestral medical traditions and the modern, westernized medical application of psychedelics. In both ancestral and modern applications, the role of set and setting, more recently framed as the therapeutic “context” (Carhart-Harris et al., 2018c) have important relationships to therapeutic benefit as well as risk. Importantly, the role of “context” resonates with developments in the science of program evaluation, in particular realist evaluation and complex interventions (Pawson and Tilley, 1997; Rog, 2012), and summarized succinctly by the phrase: “outcome = intervention + context”.

Building upon a strong foundation laid in the multidisciplinary workshop held in Tarapoto, a comprehensive evaluation protocol was developed to investigate outcomes associated with ayahuasca-assisted treatment for substance use disorders at Takiwasi Center. This institution was determined to be an excellent starting point for what was envisioned as a multi-site research project with a common protocol. Advantages associated with Takiwasi as a study site include its history of support for internally and externally driven research and evaluation, and the syncretic nature of its organizational environment and treatment program. This diversity provides fertile ground for testing a protocol designed from the outset to investigate the role of context in the determination of treatment outcomes.

The research protocol, described above in detail, is poized to make a significant contribution toward each of four study goals. Our first goal is to contribute to an understanding of ayahuasca-assisted treatment for substance use disorders. Our mixed methods approach within a longitudinal cohort design, situated in the context of complexity-based evaluation, will be critical to identifying key elements of set and setting that are most closely associated with treatment outcomes. To this end, the major strengths of the protocol include: the use of multiple, validated measures of predictors, potential moderators, and outcomes, which are assessed at multiple time points from program entry through 24 months post-discharge; multiple measures of program participation and satisfaction with services; and state-of-the-art statistical testing methods that will minimize risks of Type I error that can arise through multiple, non-theory-based significance testing. The comparative approach to addressing research questions via complementary quantitative and qualitative analytics is similar conceptually to that employed by Thomas et al. 2013 and Argento et al. (2019) in their study of ayahuasca-assisted treatment for substance use disorders in Canada, but now advantaged with a more extensive baseline assessment of patient characteristics, a larger sample size and longer follow-up period. As the current research progresses toward its first analysis and reporting on one-year follow data, it will prove to be the most rigorous and comprehensive study to date focused exclusively on ayahuasca-assisted treatment for substance use disorders.

The second study goal is to inform other potential ayahuasca-assisted treatment modalities for substance use disorders, as well as psychedelic-assisted therapy more generally. It is anticipated that the study results concerning the role of the various non-pharmacological elements of the treatment context will be useful to others that wish to incorporate this medicine into a structured treatment process. These critical ingredients may also inform the development of other psychedelic-assisted treatments for substance use and other mental health disorders as well as their evaluation. Following Carhart-Harris et al. (2018c), our findings may point to key features of treatment context worthy of pursuing with a more controlled clinical trial design; for example, music, psychotherapeutic integration, and treatment milieu. It will be particularly important to explore what aspects of the treatment model under investigation in this project might translate to more readily accessible outpatient services using ayahuasca- or other psychedelic-assisted interventions, and for whom they are most appropriate. In translating the findings to other treatment modalities, it will be important to maintain the focus on treatment set and setting as critical ingredients of the treatment intervention itself, and not viewed as an element of potential placebo to be controlled out of the outcome equation. Using our study as an illustrative case-in- point, the research is conducted in a naturalistic setting and focuses on evaluating outcomes of an integral treatment program as a whole. As such, the drinking of ayahuasca intake and subsequent experiences occur within a complex setting following the Amazonian tradition, where different practices take place (e.g., singing, application of perfumes, and perhaps intake of other psychoactive medicinal plant preparations like tobacco juice) during the same session. From a theoretical point of view, according to the cosmovision inherent in Amazonian traditional medicine, as well as the clinical experience of the Takiwasi Center, the visionary and psychedelic component of ayahuasca is not the only, nor necessarily the most important, therapeutic mediator. Indeed, Amazonian healers point emphasize the importance of the ritual as whole to trigger the healing process. Moreover, in the Amazonian indigenous and mestizo context, patients frequently do not take ayahuasca in the ceremony and it is rather just the healer who uses the psychedelic-visionary effect to facilitate diagnosis and treatment choice.

With respect to furthering work with ayahuasca or other psychedelic-assisted interventions for substance use disorders, we also advocate that close consideration be given to our comprehensive set of measures so as to facilitate cross-study comparisons. Notably, our measures map well onto the recommended outcome domains for evaluating substance use treatment (International Consortium for Health Measurement Outcomes, 2020). Further, we aim to demonstrate that situating this measurement model within a mixed methods study design will bring significant value for moving the field forward and, to this end, all measurement tools used in the study protocol are provided as easily accessible Supplementary Material, including the semi-structured interview guides. Pending resolution of importation challenges for bringing ayahuasca to Mexico for research purposes, we plan for at least one additional ATOP site, and more may eventually be added consistent with ATOP study criteria. The common measurement model and mixed methods design sets the stage for a multiple case study approach, with Takiwasi Center being the first chapter in the story of ayahuasca-assisted treatment for substance use disorders based on the ATOP protocol.

Further with respect to the ATOP measurement model, the team elected not to include measures of the immediate psychedelic (e.g., Hallucinogenic Rating Scale; Strassman et al., 1994) or “mystical/peak” experience (e.g., Revised Mystical Experiences Questionnaire (Barrett et al., 2015) to correlate with treatment outcomes. While the measurement of mystical experiences has proven valuable in lab-based clinical trials (e.g., Rothberg et al., 2021), and many other types of psychedelic research (Johnson et al., 2019), it was determined not to be a good fit for the longitudinal, naturalistic design of ATOP. From a practical viewpoint, the ayahuasca used at Takiwasi is consumed on multiple occasions from different batches, and for this reason will undoubtedly vary to some degree in pharmacological composition and effects. More important, however, is that the purpose of this study is *not* to assess specific effects of ayahuasca as a dose-response mechanism, nor aim to systematically disentangle pharmacological vs. non-pharmacological factors, but rather to evaluate an established intervention in a naturalistic setting. In this naturalistic context the mystical experience in any specific ceremony is neither necessary nor sufficient to explain outcomes associated with the multiple therapeutic aspects of treatment at Takiwasi for the duration of a patient's nine-month participation.

The third study goal is to contribute to the body of knowledge on treatment of substance use disorders and factors associated with positive treatment outcome in long-term residential treatment alternatives. In part, with this protocol we will advance understanding of the effectiveness of the long-term residential therapeutic community treatment model and its role within the overall continuum of treatment and support. In particular, we answer the call for more research on TC’s to look inside the proverbial “black box” to investigate the role of different elements of this complex treatment model in improving treatment completion and different types of outcomes. Does ayahuasca-assisted treatment within the therapeutic community model alter the trajectory of treatment completion and outcomes, and for whom? How do participants rate the importance of conventional elements of the model (e.g., treatment milieu, therapy) as compared to elements incorporated from traditional medicine and other syncretic sources? What role does spirituality play within the spectrum of outcome measures and in sustaining post-discharge improvements? For example, continuation of spiritual practices and related distinctions between safe and harmful use of psychoactive substances. What might we learn from Takiwasi’s spiritual model of addiction, including how it is operationalized through the syncretic integration of shamanic, Christian and other spiritual practices and their perceived importance in determining the outcome of treatment? Might information in this area provide insight into how the TC model, and other treatment models and modalities, could be enhanced within a broad bio-psycho-social-spiritual framework? Indeed, the results concerning the role of spirituality as a potential predictor of outcome, and as an outcome in its own right, will have implications for the field of substance use treatment writ large, given its long-standing interest in spirituality (Geppert et al., 2007; Miller and Bogenschutz, 2007).

Fourth, and last, the research protocol aims to identify strengths, challenges and limitations within the current Takiwasi treatment model so as to contribute to ongoing efforts toward quality improvement. Although a great deal of research has been supported by and undertaken by the Takiwasi Center, to date there is, no clearly documented process by which this research contributes to service enhancement. Sridharan and Nakaima (2011) speak to the strengths of realist, complexity-based evaluation in building evaluation capacity within an organization. It is with this spirit that the project team anticipates significant knowledge exchange opportunities among Takiwasi Center managers, staff, therapists, and healers to both debate the results and maximize opportunities for individual and organizational learning and growth.

